### Recruitment {15}

Participants will be recruited through our long-time collaborating network of elderly social centres in Hong Kong. Centre staff will help identify eligible individuals and refer to us for screening. The recruitment period is between January 2020 and December 2021.

## Assignment of interventions: allocation

### Sequence generation {16a}

In the randomization procedure, each participant will be assigned a special code generated by a computer (www.randomization.com). The statistician of the department will perform all the randomization.

### Concealment mechanism {16b}

Randomization will be occurred using a computer randomisation programme, so there is no human involvement, and the process will be fully concealed from both study investigators and prospective participants until the study arm is assigned.

### Implementation {16c}

The research assistants will enrol participants. The statistician of the department will generate the allocation sequence, and another independent research staff will assign participants to interventions.

## Assignment of interventions: Blinding

### Who will be blinded {17a}

Participants are assumed to be not blinded to the intervention. Nevertheless, they will be instructed not to discuss their allocation with other participants or outcome assessors. To reduce the possible expectancy bias, participants will be explained at the time of giving consent that there is no evidence to support a difference in cognitive benefit between the two arms. The research assistant who assists in consent seeking and monitoring of progress and adverse events will not be involved in outcome assessment. The assessor who will be another trained research assistant will be blinded to the randomization status and will not be involved in the intervention. The statistician responsible for the randomization is not involved in other parts of the study including data analysis.

### Procedure for unblinding if needed {17b}

In rare circumstances when the intervention has to be stopped immediately because the participant experiences an adverse event that is assessed to be related to the intervention, the principal investigator will unblind and reveal the participant’s allocation status. Unblinding will be reported to the Joint Clinical Research Ethics Committee of the Chinese University of Hong Kong and the New Territories East Cluster of the Hospital Authority.

## Data collection and management

### Plans for assessment and collection of outcomes {18a}

Screening of eligible participants, consent seeking, and cognitive outcome assessments will be performed by trained research assistants in our research centre, whereas the MRI brain scan will be performed in the teaching hospital.

A screening checklist will be used to ensure that the eligible individuals fulfil all the inclusion criteria and do not meet the exclusion criteria. Also, the number of years and the average number of hours/week of calligraphy practice that our participants have prior to joining this study will be recorded.

The cognitive outcomes and the resting-state functional connectivity, together with the covariables, will be assessed before (T0) and after the intervention (T1). Adverse events will be assessed at T1. The assessment schedule is shown in Table 1.

**Table 1 Tab1:** Assessment schedule

Assessment	Baseline	Follow-up
Alzheimer’s Disease Assessment Scale-Cognitive Subscale	✓	✓
Montreal Cognitive Assessment	✓	✓
Memory Inventory for Chinese	✓	✓
Digit Span Forward	✓	✓
Digit Span Backward	✓	✓
Trail making test—Part A	✓	✓
Trail making test—Part B	✓	✓
10-min delayed recall test	✓	✓
Chinese verbal fluency test	✓	✓
Sociodemographic factors	✓	✓
Chronic Illness Rating Scale	✓	✓
Lifestyle Questionnaire	✓	✓
Neuroimaging	✓	✓
Adverse events		✓

To ensure the quality of our data (e.g. to identify any double data entry and any outliers), both the trained research assistants and the principal investigator will independently perform data cleansing before data analysis begins.

### Plans to promote participant retention and complete follow-up {18b}

To promote adherence of calligraphy practice during the 6-month intervention period, participants from both groups will be asked to use WhatsApp or email the research assistant a snapshot of their work and the amount of time they spend in calligraphy each time they finish practising. Upon receiving their work, the research assistant will acknowledge receipt of their work and log but will not give them any feedback on their work. Those who do not have smartphones or internet access will be asked to record in a diary the date and amount of time spent on their work each time they finish practising calligraphy, and to hand in their diary and work to the research assistant bi-monthly for review of adherence. Although any participant is free to withdraw from the study at any time without giving a reason, they will be asked whether they wish to be followed up according to the study schedule.

### Data management {19}

Electronic data entry will be used. The trained research assistants will collect and enter the data. Data cleansing will be performed by trained research assistants and principal investigator independently. Data will be anonymized and kept in password-protected computers. Only the principal investigator, co-investigators, and authorized research assistants will have access to the personal data during and after the study. Data management procedures are documented in the ethics application, which has already been approved by the ethics committee (Joint Chinese University of Hong Kong – New Territories East Cluster Clinical Research Ethics Committee; reference number: 2019.054).

### Confidentiality {27}

Personal identifier will not be collected in this study. The anonymized data that supports the findings of this study will be available from the principal investigator upon reasonable request. The data will be kept for 5 years after completion of study and related publications. The data will then be deleted.

### Plans for collection, laboratory evaluation and storage of biological specimens for genetic or molecular analysis in this trial/future use {33}

See above {26b} there will be no biological specimens collected.

## Statistical methods

### Statistical methods for primary and secondary outcomes {20a}

Statistical analysis will be performed using IBM SPSS Statistics for Windows. Independent *t* test (for continuous variables) and chi-square test (for categorical variables) will be used to compare socio-demographics, clinical characteristics, lifestyle activities, cognitive functions, and resting-state FCs at baseline between the control and intervention groups for exploratory analyses. Repeated measures analysis of variance will be used to evaluate the cognitive and FC changes, with time being the within-group factor, control/intervention as the between-group measure, and covariates being controlled for. Association between cognitive parameters and FCs will be computed with correlational analyses. Intention-to-treat analysis and Bonferroni correction will be adopted.

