### Sample size {14}

#### Cognitive function

The sample size (alpha 0.05, power 0.80) required to detect significant differences in global cognitive function over 6 months as assessed by ADAS-Cog between intervention and control groups is estimated using G*Power 3.1. Based on a similar RCT of 8-week calligraphy training in local older people with MCI living in care homes [26], the effect size (ES) on cognitive outcome was estimated to be 0.56. However, because the participants of this study are younger, less frail, living actively in the community, and at an earlier stage of AD, a relatively larger cognitive response (ES=0.70) is anticipated as suggested by a previous review of complex mental activity on cognition [46]. Nevertheless, because the control group will have ongoing calligraphy practice, the additional cognitive benefits arising from doubling the participation in calligraphy in the intervention group is anticipated to be lowered by a conservative estimate of 50%. Taking into consideration the effect of covariates on the cognitive outcome and an estimated drop-out rate of 20%, a total of 112 participants will be required for this study.

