### Methods for additional analyses (e.g. subgroup analyses) {20b}

Sensitivity analysis will be performed for participants who complete the intervention and all assessments, and a secondary analysis will be conducted to identify any differences in the effect of intervention among participants with different amounts of calligraphy practice at baseline.

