### Methods in analysis to handle protocol non-adherence and any statistical methods to handle missing data {20c}

In our electronic data entry, the record cannot be submitted unless all the data have been entered, thus minimizing missing data. Adherence to intervention, which is recorded by our trained research assistants on a weekly basis, serves as a covariate and will be included in the data analysis.

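### The analysis is labelled intention-to-treat, but the two-time-point repeated-measures ANOVA uses only participants with a 6-month assessment and does not condition on baseline score, and the missing-data section does not cover an absent follow-up

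*Protocol article*

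**What the plan says.** All references are to the protocol article.

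- **Model and principle, {20a}.** "Repeated measures analysis of variance will be used to evaluate the cognitive and FC changes", in SPSS, with time as the within factor, arm as the between factor and covariates controlled for. The same paragraph ends: "Intention-to-treat analysis and Bonferroni correction will be adopted".
- **Assessment times, {18a} and Table 1.** Cognition and imaging are measured twice, at baseline (T0) and after the intervention (T1). There is no intermediate visit.
- **Expected loss, Sample size {14}, Cognitive function.** The total allows for "an estimated drop-out rate of 20%, a total of 112 participants will be required for this study".
- **Missing data, {20c}.** The provision on incomplete data is that "the record cannot be submitted unless all the data have been entered, thus minimizing missing data". The section otherwise adds adherence as a covariate.
- **Sensitivity analysis, {20b}.** "Sensitivity analysis will be performed for participants who complete the intervention and all assessments".
- **Withdrawal, {18b}.** Of participants who withdraw: "they will be asked whether they wish to be followed up according to the study schedule". Follow-up is offered but optional.
- **Covariates, {12}.** Sociodemographic factors, comorbidity, health behaviours and adherence are listed. The baseline value of the outcome is not.

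**The concern.** The plan sets an intention-to-treat label beside a model that, run as named, has no place for a randomised participant without T1. The section meant to deal with missing data answers a different problem: it prevents empty fields in a record that somebody is completing, and does nothing for a visit that never takes place. Yet the sample size section expects losses of just this kind.

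Two things are at stake. First, a result could be reported as intention-to-treat when it rests on participants with both assessments. Second, the arms make different demands: one doubles its practice time for six months and the other changes nothing, and participants know their allocation. Different people may therefore leave each arm. Unequal drop-out rates alone do not bias the contrast, but drop-out that is related to the score does. A change-score comparison is exposed even in the simple case where drop-out depends only on the baseline score, which is observed for everyone.

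**Working it through.** **1. Who is in the analysis.**
Inputs: 112 randomised, 20% drop-out ({14}).
- The plan's own inflation: 90 / 0.80 = 112.5, so 112 matches about 90 analysed. Only this drop-out step is used here; the route from the effect size to about 90 is a separate matter.
- 112 × 0.80 = 89.6, so about 90 have both assessments.
- 112 × 0.20 = 22.4, so up to about 22 do not.

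The figure of 22 is an upper planning value. It assumes that nobody who drops out accepts the follow-up offered in {18b}.

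**2. What the model tests.** With two time points, the arm-by-time test in repeated-measures ANOVA is the comparison of T1 − T0 between arms. Covariates adjust that change, but the baseline score is not among them. A participant without T1 has no change score.

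**3. What the sensitivity analysis adds.** The {20b} set requires completion of the intervention and of all assessments. It is a subset of those with T1: it further removes people who were assessed but did not complete the intervention. Nobody without T1 is in either set.

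**4. Size of the bias when drop-out depends on baseline (assumed illustration).**
None of these inputs is in the protocol:
- 56 per arm, no true effect, outcome SD 1, higher = worse;
- baseline to follow-up correlation r = 0.5 or 0.7;
- control drop-out 12% at random;
- intervention drop-out with logit −1.2 + 1.0 × baseline, which gives about 27%.

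Overall loss is (27% + 12%) / 2 = 19.5%, in line with the planned 20%. Intervention drop-outs are on average 0.62 SD worse at baseline, so those who stay are better than the arm as randomised by

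0.27 × 0.62 / 0.73 = 0.229 SD.

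They regress towards the mean. Their expected change is (1 − r) × 0.229 in the worse direction, while control completers have expected change 0:

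| r | Bias by formula | Simulated change-score bias | Simulated bias conditioning on baseline |
|---|---|---|---|
| 0.5 | 0.5 × 0.229 = 0.115 | 0.11 | about 0 |
| 0.7 | 0.3 × 0.229 = 0.069 | 0.07 | about 0 |

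The planned effect is 0.70 × (1 − 0.50) = 0.35. The bias is therefore 0.07 / 0.35 = 20% to 0.11 / 0.35 = 31% of it. It runs **against** the intervention. If participants with better baseline scores left instead, the sign would reverse.

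**5. Drop-out that depends on the unseen outcome (assumed illustration).** Suppose 20% drop out in each arm and, in one arm only, drop-outs differ from completers in mean change. Then bias = drop-out share × difference:
- 0.20 × 0.25 = 0.05 SD (0.05 / 0.35 = 14%);
- 0.20 × 0.75 = 0.15 SD (0.15 / 0.35 = 43%).

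To the extent that this difference is not explained by baseline or covariates, conditioning on baseline does not remove it. That is why a separate sensitivity analysis is needed.

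**The case against.** The strongest reply is that this is a condensed article. It does not say that participants without T1 are deleted; repeated-measures ANOVA can be run on imputed data, and an intention-to-treat commitment might imply such a step in a fuller document. That is fair as regards the imputation method, whose absence alone would be no finding. But the article names the model and gives its own answer under the missing-data heading, and that answer does not reach an absent T1. The point rests on what is stated.

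Other parts of the reply stand and limit the point:

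- **Loss of 22 is not a forecast.** A reader might take it that 22 people will be excluded. The 20% is a sample size allowance, and {18b} treats withdrawal and loss of follow-up as separate events.
- **The completer analysis is not empty.** A reader might infer that it tests nothing. It also removes people with T1 who did not complete the intervention, so it does contrast as-randomised with completing participants. What it cannot do is probe the missing-data assumption.
- **Forced entry need not destroy valid scores.** A reader might infer that a failed scan would block a valid ADAS-Cog. Section {20c} does not say that cognition and imaging share one record, and {18a} places them at different sites, so the documents do not support this.
- **The illustration favours conditioning on baseline.** The bias in step 4 also vanishes in a completer analysis adjusted for baseline. The numbers therefore support that adjustment more than they support retaining all 112.

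**Conclusion.** The point holds in this form. As written, the plan declares intention-to-treat but names a model that by default analyses only those with both assessments and does not condition on the baseline score. Its missing-data provision does not cover an absent T1, and its sensitivity analysis shares the same gap. Up to about 22 of 112 participants are affected.

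The bias of 0.07 to 0.11 SD (20% to 31% of the planned 0.35) rests on assumed drop-out rates, an assumed dependence on baseline in one arm and assumed correlations of 0.5 to 0.7. It shows how large the problem could be, not that it will occur. A reader might infer a risk of a falsely positive trial. The case worked here shows the opposite, a benefit diluted or hidden, and the documents give no basis for predicting either direction. The sample size is not affected, because the inflation already leaves about 90 for analysis.

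**What to change.** In {20a}, replace repeated-measures ANOVA with a likelihood-based linear mixed model (SPSS MIXED):

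- T0 and T1 scores as outcomes, a common baseline mean for the two arms, an arm-by-time effect and covariates measured at baseline;
- every randomised participant with any assessment included, as randomised, among them those who stop practising.

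The common baseline mean supplies the conditioning on baseline. The model is valid if drop-out depends only on observed baseline data and arm.

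In {20b}, keep the completer set as a sensitivity analysis and describe it as such. Add one analysis for informative drop-out, delta-adjusted or reference-based, with its settings fixed before the data are analysed. In {20c}, state how an absent T1 is handled, separately from blank fields.

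The cost is new wording and a little more analysis work in the same software, with no change to sample size or visits. With a single follow-up, participants who have only a baseline add little information, so little power is gained. The gain is in validity and in an accurate intention-to-treat label.

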### Intervention description {11a}

Participants will be randomized in a 1:1 ratio to one of the following arms.
Control group: Participants will continue their usual practice of calligraphy in the same manner (i.e. same frequency, duration, style, and environment).Intervention group: Participants will continue their usual practice of calligraphy in the same manner, with the exception of doubling the amount of time spent in calligraphy.

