#### Covariates

Sociodemographic factors (age, sex, educational level, occupational attainment, employment status, marital status, and social network), physical comorbidities (as assessed by Chronic Illness Rating Scale), health behaviours (smoking and drinking, type and amount of other leisure activities, including social, physical, recreational, and intellectual activities, as assessed by Lifestyle Questionnaire [45]), and adherence to intervention (assessed based on the records of their work) will also be measured and included in the analysis.

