#### Functional connectivity

The sample size is calculated based on a RCT of cognitive training on memory in people with MCI (*n*=72) in which individual FC maps for the hippocampal seed were generated based on correlations between the mean signal time course within each seed region and the rest of the brain [47]. Cognitive training was found to increase FC between the hippocampus and left superior frontal lobe compared to sham, and a positive correlation (*r*=0.33; *p*=0.005) between changes in hippocampal FC and changes in the memory domain was identified. Therefore, we estimate that a sample of 70 will achieve a power of 0.80 with alpha 0.05 (two-tailed). Assuming the same dropout rate, our initial calculation of 112 participants will yield enough power for the FC-cognition analysis.

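### The two-time-point repeated-measures ANOVA is valid but less precise than modelling the 6-month score with the baseline score as a covariate; changing it needs no new data

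*Protocol article*

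**What the plan says.** Section {20a} names one model for the cognitive and functional connectivity outcomes, a repeated-measures ANOVA "with time being the within-group factor, control/intervention as the between-group measure, and covariates being controlled for". The Methods part of the abstract names the same model. Section {18a} and Table 1 give two assessments, T0 before and T1 after the 6-month intervention.

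The covariates are listed in the abstract and under Covariates in section {12}. Neither list contains the baseline value of the outcome, so the T0 score enters as one of the two repeated outcome values. For activities, the Covariates list covers "type and amount of other leisure activities, including social, physical, recreational, and intellectual activities". It also includes adherence, which arises after randomisation.

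Section {18a} states that "the average number of hours/week of calligraphy practice that our participants have prior to joining this study will be recorded". The only analysis that refers to these hours is the secondary one in {20b}, intended to "identify any differences in the effect of intervention among participants with different amounts of calligraphy practice at baseline".

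**The concern.** With two time points, the repeated-measures ANOVA fixes the coefficient of the baseline score at 1. ANCOVA estimates that coefficient from the data and so leaves less residual variance whenever r is below 1.

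This matters because the sample size section relies on covariates for precision. Under Cognitive function in {14}, the total of 112 is said to allow for the effect of covariates on the outcome, with no figure attached. The baseline score is a natural candidate for that role, and the model in {20a} does not use it as efficiently as it could. What is at stake is power for the primary ADAS-Cog comparison and, by the same algebra, for the connectivity comparisons.

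**Working it through.** **Inputs.**
- Error rates, from the cognitive part of section {14}: "The sample size (alpha 0.05, power 0.80) required to detect significant differences in global cognitive function over 6 months as assessed by ADAS-Cog". Sidedness is not stated there. I take it as two-sided, as in the connectivity calculation that follows it.
- Effect size, same section: "a relatively larger cognitive response (ES=0.70) is anticipated", then halved because the control group also practises, giving d = 0.35.
- Evaluable sample: 112 × 0.80 = 89.6, about 90, or 45 per arm at 1:1 allocation.
- T0–T1 correlation r: not given, so assumed from 0.3 to 0.9.

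**The plan's own figure.** For d = 0.35 with no covariate gain, n per arm = 2(1.960 + 0.842)²/0.35² = 128.1. This rounds up to 129 per arm, or 258 evaluable, and 258/0.80 = 322.5, so 323 recruited. The stated 112 is not reproduced from the quantified inputs. About 90 evaluable would need covariates explaining roughly 1 − 90/258 = 0.65 of the outcome variance. The missing input is a separate matter. It is relevant here because it shows how far the design relies on covariate precision.

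**Variances.** Assume equal variance (set to 1) at T0 and T1.
- Change score: Var(T1 − T0) = 2(1 − r).
- ANCOVA residual: 1 − r².
- Ratio: (1 − r²)/[2(1 − r)] = (1 + r)/2, which is below 1 for every r < 1.

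**Power.** Noncentral t with noncentrality d·√(45/2)/√(variance factor), on 88 degrees of freedom for change and 87 for ANCOVA. At r = 0.5 the noncentrality is 0.35 × 4.743/√1.00 = 1.660 for change and 0.35 × 4.743/√0.75 = 1.917 for ANCOVA.

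| r | Change factor | ANCOVA factor | Ratio | Power, change | Power, ANCOVA |
|---|---|---|---|---|---|
| 0.3 | 1.40 | 0.91 | 0.65 | 0.28 | 0.41 |
| 0.5 | 1.00 | 0.75 | 0.75 | 0.38 | 0.47 |
| 0.7 | 0.60 | 0.51 | 0.85 | 0.56 | 0.63 |
| 0.8 | 0.40 | 0.36 | 0.90 | 0.74 | 0.78 |
| 0.9 | 0.20 | 0.19 | 0.95 | 0.96 | 0.96 |

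The evaluable total for power 0.80 is 260 against 196 at r = 0.5, 156 against 134 at r = 0.7, and 106 against 96 at r = 0.8 (change against ANCOVA).

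**Simulation check.** In 20,000 trials of 45 per arm, the variance ratios were 0.76 (r = 0.5) and 0.86 (r = 0.7). Rejection rates were 0.38 against 0.47 and 0.56 against 0.63. Both methods recovered the true difference of 0.35 on average.

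**Other scale for 0.35.** If 0.35 is in standard deviations of change, power of the change test is 0.38 at every r, and the ANCOVA noncentrality is 1.660 × √[2/(1 + r)]. At r = 0.7 that is 1.801, with power 0.43.

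**Adding baseline hours.** Suppose hours explain a further share of the variance left after T0. The ANCOVA factor becomes (1 − r²)(1 − share). For shares of 0, 0.02, 0.05 and 0.10, power is 0.474, 0.482, 0.494 and 0.515 at r = 0.5, and 0.633, 0.641, 0.655 and 0.678 at r = 0.7.

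**The case against.** The strongest reply is that nothing in {20a} is wrong. The section sets out to evaluate change, and in a randomised trial the group-by-time test does that without bias. It also uses the baseline score, with its coefficient fixed at 1. All of that stands: the loss is of efficiency only.

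The size is also uncertain. The protocol gives no T0–T1 correlation, and at r = 0.9 the two analyses hardly differ. The figures depend on the scale of the 0.35. They also leave out the other planned covariates, which would enter both models. That does not remove the difference: r then becomes the correlation after adjustment for those covariates and, with equal residual variances, the ratio keeps the same form.

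A reader might infer three stronger criticisms that the protocol does not support.
- *The treatment test is a group main effect diluted by a pre-treatment value.* Section {20a} does not name that effect as the test, and its stated purpose is change.
- *The secondary analysis in {20b} splits participants at an unstated cut-point.* The text mentions neither groups nor a cut-point, and it is compatible with a continuous interaction.
- *Baseline hours are the most prognostic variable.* It is true that the added dose depends on a participant's own habit, since the intervention group continues as usual "with the exception of doubling the amount of time spent in calligraphy". But no figure in the protocol shows that hours predict the outcome. Chance imbalance in hours is already allowed for in the error rate of a randomised comparison.

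**Conclusion.** The point holds as a free improvement, not as an error. The fixed model amounts to a change-score comparison, and ANCOVA on the 6-month score has a smaller variance for every r below 1, apart from the one degree of freedom spent. With d = 0.35 in T1 standard deviations and 45 per arm, the gain is about 12 percentage points of power at r = 0.3, 10 at r = 0.5, 7 at r = 0.7, 4 at r = 0.8 and at most 1 at r = 0.9. If 0.35 is on the change scale, the gain at r = 0.7 is about 5 points.

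These figures assume equal variances at the two visits and a correlation that the protocol does not supply. The direction needs only the equal variances and r below 1. The gain from baseline hours is weaker: nil if hours do not predict the outcome given the baseline score, and about 1 to 5 points for an assumed further share of 0.02 to 0.10.

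**What to change.** In {20a}, make the primary model the 6-month score on arm, with the baseline score of the same outcome and the planned baseline covariates at their T0 values. A mixed model with the baseline means constrained equal between arms is an equivalent choice. Name the arm coefficient as the treatment test, and use the same form for the connectivity outcomes.

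Optionally, add baseline calligraphy hours per week as a covariate. They are already recorded under {18a}, but the Covariates list, limited to other leisure activities, leaves them out.

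The cost is a wording change, one model degree of freedom for the baseline score and one more if hours are added. No new data, visits or participants are needed. Under {25} the change goes to the ethics committee, and it should be dated before the final analysis.

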### Trial design {8}

This study is a two-arm, parallel-design, single-blind RCT of 6-month calligraphy practice conducted in Hong Kong. Participants will be randomized in a 1:1 ratio to either the intervention or control group. The framework of our trial is to test the superiority of doubling the “dosage” of calligraphy practice (*vs* maintaining on the same “dosage”) on cognitive function and FC of DMN.

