#### Secondary cognitive outcomes

To increase the sensitivity of detecting important cognitive changes in our participants, additional assessments will be performed to assess the global and specific cognitive domains. Global cognition will be assessed by the HK-MoCA, a locally validated cognitive screening test to detect early memory and executive deficits in MCI [27], and the Memory Inventory for Chinese (MIC), which is a locally validated 27-item questionnaire on detecting SCD [31]. Regarding the specific cognitive domains, attention will be assessed by the digit span forward (DSF) test and the part A of trail making test (TMT-A); learning and memory will be assessed by the 10-min delayed recall and digit span backward (DSB) tests; and executive functioning will be assessed by the part B of trial making test and the Chinese verbal fluency test (CVFT) [32–36].

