##### FC analysis

Given the functional anatomy of DMN [18, 40], five pairs of brain areas are selected as regions of interest (ROIs): IPL, mPFC, HF+, PCC, and LTC. The masks of ROIs were generated by the WFU Pick Atlas (http://fmri.wfubmc.edu/software/PickAtlas) corresponding to the anatomical regions embedded in the automated anatomical labelling (AAL). The mean time courses are extracted from each ROI by averaging the time courses over all voxels within the ROI. To better illustrate the functional organization of DMN subregions, whole-brain and ROI-wise FC will be employed. For whole-brain FC, Pearson correlation coefficients will be calculated between each ROI and the whole brain areas embedded in the AAL atlas [41]. After Fisher’s *z* transformation, an individual FC map will be used for group-wise comparison. For ROI-wise FC, Pearson correlation coefficients will be calculated between the corrected time series of the ROIs. The absolute value of the correlation coefficient (*r*) will be used as a measure to evaluate the FC between the ROIs [42–44]. Smaller value of FC indicates decreased connectivity between DMN subregions.

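### Optional improvement: Holm's step-down procedure could replace plain Bonferroni, with the same family-wise error control and a small gain in power that depends on the family

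*Protocol article*

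**What the plan says.** The only statement on multiplicity is one clause in Statistical methods {20a}: "Intention-to-treat analysis and Bonferroni correction will be adopted". It gives no family, no number of tests, and no word on whether the correction is single-step or step-down. Unqualified, the term normally means the single-step rule, in which each of m tests is judged at alpha/m.

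Several sets of tests could form a family:

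- **Cognitive.** ADAS-Cog is the primary cognitive outcome. Under Secondary cognitive outcomes, "additional assessments will be performed to assess the global and specific cognitive domains"; eight scores are listed (HK-MoCA, MIC, digit span forward and backward, trail making A and B, delayed recall, verbal fluency).
- **Imaging.** Under FC analysis, "five pairs of brain areas are selected as regions of interest (ROIs): IPL, mPFC, HF+, PCC, and LTC". Counting each named region once gives 5 × 4 / 2 = 10 region-to-region links.
- **The two primaries.** One cognitive and one neuroimaging outcome are each labelled primary.

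For scale, the Sample size section on cognitive function works at alpha 0.05 and power 0.80. It starts from an effect size of 0.70 ("a relatively larger cognitive response (ES=0.70) is anticipated") and says that the added benefit of doubling practice "is anticipated to be lowered by a conservative estimate of 50" per cent. It ends with "an estimated drop-out rate of 20%, a total of 112 participants will be required for this study". Allocation is 1:1.

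**The concern.** Single-step Bonferroni holds every test to alpha/m, even after other hypotheses in the family have been rejected. Holm's procedure relaxes the threshold after each rejection and keeps the same error guarantee. Where the plan has several tests per family and expects an effect on more than one, the single-step rule gives up some power on the second and later findings without a lower guaranteed error rate.

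This matters mainly for statements about individual cognitive domains or individual network links, which depend on rejections beyond the first. It does not affect whether the trial finds anything at all within a family.

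**Working it through.** **Plan figures.** The article gives no figure for power after correction, so there is none to reproduce on this point. The total of 112 can be neither confirmed nor refuted, because the size of the covariate effect is not given.

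**Inputs.** Completers: 112 × 0.8 = 89.6, about 90, so 45 per arm at 1:1. Effect: 0.70 × 0.5 = 0.35, read as Cohen's d (the article does not say which effect-size metric it uses). Two-sided alpha 0.05 (assumed, since sidedness is not stated for the cognitive outcome). Correlation 0.4 between outcomes (assumed). Families of 2, 8 and 10 (assumed). Two-sample t tests without covariates.

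**Why Holm dominates.** Order the p-values p(1) ≤ … ≤ p(m). Bonferroni rejects any p ≤ α/m. Holm goes up the list and rejects p(j) while p(j) ≤ α/(m − j + 1).

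- Since α/(m − j + 1) ≥ α/m at every step, everything Bonferroni rejects, Holm rejects.
- With m₀ true null hypotheses, the first false rejection comes at step m − m₀ + 1 at the latest, so it needs a true-null p-value ≤ α/m₀. The chance of that is at most m₀ × α/m₀ = α, whatever the dependence.
- Holm's first threshold is α/m, the same as Bonferroni's. The chance of at least one rejection is therefore identical.

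**Bonferroni power by formula, d = 0.35.** The noncentrality is 0.35 × √(45/2) = 1.66. For m = 2 the normal approximation gives Φ(1.66 − 2.24) = 0.28, and the exact noncentral t gives 0.27. For m = 8 the exact value is 0.13.

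**Simulation (8,000 replicates; a repeat with 40,000 agrees to about 0.01).** Mean power per real effect:

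| Assumed family | Real effects | d | Bonferroni | Holm |
|---|---|---|---|---|
| 8 secondary cognitive tests | 8 | 0.35 | 0.13 | 0.16 |
| 8 | 4 | 0.35 | 0.13 | 0.14 |
| 2 | 2 | 0.35 | 0.27–0.28 | 0.31 |
| 8 | 8 | 0.50 | 0.34 | 0.42 |
| 8 | 8 | 0.60 | 0.52 | 0.63 |
| 8 | 4 | 0.60 | 0.52 | 0.55 |
| 10 network links | 10 | 0.60 | 0.50 | 0.61 |
| 2 | 2 | 0.60 | 0.71 | 0.77 |

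In the family of two with both effects real, the chance of confirming both rises from 0.12–0.13 to 0.19 at d = 0.35, and from 0.55 to 0.67 at d = 0.60. Family-wise error stayed at or below 0.05 for both methods. In every replicate of the repeat run, Holm rejected everything that Bonferroni rejected, and the two agreed on whether anything was rejected.

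**Second setting (200,000 replicates).** Each real effect was given 80% unadjusted power, with correlation 0 or 0.5. In a family of 10, Bonferroni to Holm goes from about 50% to 50.5% with 2 real effects, from 50% to 53% with 5, and from 50% to 61% with all 10. In a family of 2 with only one real effect it goes from 71.3% to 71.5% at most. The gain is negligible when few effects are real.

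**The case against.** The strongest reply is that nothing here is wrong. Bonferroni is valid, conventional and conservative, and it protects the error rate it is meant to protect. It also gives fixed thresholds and simultaneous confidence intervals that match the tests, which Holm does not give directly. All of that stands, and it is why this is an optional improvement and not a defect.

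Three stronger readings are tempting, and the article does not support them:

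- **That power is lost for nothing.** The matching intervals are a real return, and at the effect the plan anticipates the loss is small.
- **That the plan applies a single-step correction to eight cognitive scores and to a given number of network links.** The clause names neither the form nor the family. The full protocol or analysis plan may define both.
- **That the correction contradicts the plan's wish for greater sensitivity under Secondary cognitive outcomes.** That remark explains why more instruments were added. It says nothing about rejection thresholds.

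It is also fair to object that the simulation uses plain t tests, whereas the plan uses repeated-measures analysis of variance with covariates. Covariates would raise power under both methods by an amount the article does not give, so the size of the gain is illustrative. The dominance itself does not depend on the test used, provided the p-values are valid.

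**Conclusion.** The point holds as a cheap, optional improvement. Holm keeps the same family-wise error control under any dependence and never rejects fewer hypotheses, whatever family is intended. At d = 0.35 the gain is about 1 to 3 points of mean power per real effect when half or all of the assumed eight are real, and about 3 points in a family of two with both real. Gains of about 11 points need effects near d = 0.60 on all outcomes of a family of eight or ten. With few real effects the gain is 0 to 1 point.

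These sizes rest on the assumed families, 45 completers per arm, correlation 0.4 and unadjusted t tests. A primary outcome tested alone is unaffected.

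A reader might infer that Holm would also reconcile the planned correction with the sample sizes, which use alpha 0.05 without adjustment ("The sample size (alpha 0.05, power 0.80) required to detect significant differences in global cognitive function over 6 months"). It would not: Holm's first step uses the same alpha/m as Bonferroni.

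**What to change.** In Statistical methods {20a}, replace the reference to Bonferroni correction with: *Holm's step-down Bonferroni procedure within each family of tests*. Fix this before the unblinded analysis.

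The cost is one phrase. It uses the same p-values and needs no new data, and no stated sample size, alpha or power changes. The one downside is that simultaneous confidence intervals are less direct under Holm. Bonferroni or unadjusted intervals can be shown alongside, labelled as such.
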